### Primary outcome measure

The primary outcome measure is aortic distensibility. It will be measured and quantified at baseline and at one year in each arm of the study. Increased arterial stiffness is associated with an increased risk of CV events [9]. It can be measured by pulse wave velocity or as distensibility of the aorta, but requires careful correction for age and blood pressure. It has previously been shown that aortic distensibility relates to clinical outcome and that TNFi improve aortic distensibility [27]. We performed a pilot study in 10 patients with RA (disease duration 20 ± 9.6 years) and matched by age and gender to 10 asymptomatic subjects without RA. Aortic distensibility was significantly different in RA patients, with a mean and standard deviation of 1.83 ± 0.4 cm^2^ versus 2.6 ± 0.6 cm^2^ in controls. LV volumes and mass were similar between groups and LV strain and twist showed trends towards a reduction in RA patients, but without reaching statistical significance. Our pilot data therefore suggested CV abnormalities in patients with RA in several quantitative CMR parameters, with aortic distensibility reaching statistically significant difference even in the small sample size.

Longitudinal changes of outcome measures in response to therapy will be measured and compared between the two treatment arms at baseline, one and two year time points. Secondary outcome measures are i) myocardial perfusion reserve, ii) LV strain and twist, iii) LVEF and iv) LV mass. Exploratory outcome measures are pre- and post-contrast T1 mapping, extra-cellular volume (ECV) and biomarker measurements.

Significant differences (expressed as *P* <0.05) of CV abnormalities detected by CMR between the two treatment arms will be presented, and the magnitude of this difference will be expressed as a 95% confidence interval.

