Both treatment arms will be compared with primary outcome aortic distensibility from baseline to one-year follow-up, as well as other outcome measures. Analysis will be conducted in the R environment for statistical computing (R Core Team, 2012. R: A language and environment for statistical computing. R Foundation for Statistical Computing, Vienna, Austria). Exploratory data analysis will be used to determine if parametric (independent samples Student’s t-test) or non-parametric (Wilcoxon rank sum test) analyses are appropriate, and to summarize the distribution of aortic distensibility and change in other outcome measures across the two treatment arms. These analyses will also allow the credibility of an equal variance assumption to be assessed in parametric modeling and to be appropriately modeled [42]. All patients meeting eligibility criteria will be included in the analyses and these will be conducted at the end of the recruitment period. Exploratory subgroup analyses will be conducted separately by other comorbidities, a maximum of two to three that are clinically plausible, with appropriate correction for multiple testing [43]. Interactions between subgroups and interactions between CMR findings and biomarkers will be explored through building a linear model with interaction terms [44]. Patterns of CVD pathology in RA patients will be described. Treatment effects on secondary outcome measures and effects at the two-year follow-up point will be analyzed in an equivalent manner.

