### CMR image analysis and reporting

Image analysis will be performed offline, blinded to patient characteristics and treatment arm, using commercially available software (cvi42 version 4.1.3, Circle Cardiovascular Imaging Inc., Calgary, Canada and inTag version 1.0, CREATIS lab, Lyon, France) according to international standards for reporting of CMR studies [54].

LV volume and EF will be calculated from the short axis cine-stack using standard criteria to delineate cardiac borders [54]. Regional wall motion in 17 cardiac segments will be graded visually. Aortic cross sectional measurements will be made by manual planimetry of the endovascular-blood pool interface, at the times of maximal and minimal distension of the aorta. Aortic distensibility, compliance and stiffness index are calculated by standard methods using blood pressure measurements taken at the time of image acquisition with formulas and definitions listed in Table 2
[55].

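### The primary test is chosen from the data with no stated rule, and neither candidate adjusts for baseline distensibility, age or blood pressure level

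*Protocol article*

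**What the plan says.** The Primary outcome measure section makes aortic distensibility the primary outcome and says of it: "It will be measured and quantified at baseline and at one year in each arm of the study". A baseline value is therefore planned for every patient. The same section says that arterial stiffness can be measured as pulse wave velocity or distensibility, "but requires careful correction for age and blood pressure". On reporting, it says that "the magnitude of this difference will be expressed as a 95% confidence interval".

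The analysis is described in the Sample size calculation section. The contrast is worded: "Both treatment arms will be compared with primary outcome aortic distensibility from baseline to one-year follow-up". The test is left open: "Exploratory data analysis will be used to determine if parametric (independent samples Student’s t-test) or non-parametric (Wilcoxon rank sum test) analyses are appropriate". The variance assumption is also judged from the data: "These analyses will also allow the credibility of an equal variance assumption to be assessed in parametric modeling". The only linear model in the article is for exploratory work on subgroups and biomarkers, where interactions "will be explored through building a linear model with interaction terms". Secondary outcomes and two-year effects are to be handled in the same way as the primary outcome.

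Blood pressure appears in one other place. Under CMR image analysis and reporting, distensibility is derived "using blood pressure measurements taken at the time of image acquisition", and Table 2 gives the formula as ΔD/(ΔP × D).

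**The concern.** There are two linked problems.

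**The estimand is not fixed.** A t-test addresses a difference in means and a rank-sum test addresses a shift in ranks. Exploratory analysis picks between them after the distributions in the two arms have been summarised, and no criterion is given. The wording also leaves unclear whether the tested quantity is the one-year value or the change from baseline. The sample size, by contrast, is built on a mean difference of 2.46.

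**The adjustment that the article calls for is absent from the comparison.** It says the measure needs correction for age and blood pressure, then names two tests that take no covariates. The baseline scan is used at most through a change score.

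At stake are the precision of the primary estimate, its exposure to chance imbalance between small arms, and the reader's confidence that the primary test was settled independently of the result.

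**Working it through.** **Inputs from the Sample size calculation section:** effect 2.46, SD 3.5 (both in cm² dyne⁻¹ 10⁻⁶), two-sided 5% level, and 26, 33 and 44 per arm for 70%, 80% and 90% power. The correlation r between baseline and one-year distensibility is not given. I assume 0.3, 0.5 and 0.7, and equal SDs at the two times.

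**1. Reproduce the plan.** The standardised effect is 2.46/3.5 = 0.703. A two-sample t-test (noncentral t) needs 25.98, 32.76 and 43.52 per arm, which round up to 26, 33 and 44. This matches the article, so the sample size rests on an unadjusted t-test.

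**2. Power at 33 per arm if 3.5 is the SD of one-year values.** The article supports this reading, because it derives 3.5 from the SD of post-treatment measurements (3.2).
- Follow-up only: SD = 3.5.
- Change score: SD = 3.5 × √(2(1 − r)).
- Baseline-adjusted model (ANCOVA): residual SD = 3.5 × √(1 − r²).

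| r | Change SD | ANCOVA SD | Power, change | Power, follow-up only | Power, ANCOVA |
|---|---|---|---|---|---|
| 0.3 | 4.14 | 3.34 | 66% | 80% | 84% |
| 0.5 | 3.50 | 3.03 | 80% | 80% | 90% |
| 0.7 | 2.71 | 2.50 | 95% | 80% | 98% |

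**3. Power at 33 per arm if 3.5 is the SD of change.** The ANCOVA variance is (1 − r²)/(2(1 − r)) = (1 + r)/2 of the change-score variance, so the residual SD is 3.5 × √((1 + r)/2).

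| r | ANCOVA SD | Power, change | Power, ANCOVA |
|---|---|---|---|
| 0.3 | 2.82 | 80% | 94% |
| 0.5 | 3.03 | 80% | 90% |
| 0.7 | 3.23 | 80% | 86% |

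ANCOVA has the highest power in every row of both tables. These figures ignore the few degrees of freedom that covariates use. Age and blood pressure may add precision, but the article gives nothing from which to size that.

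**4. Chance imbalance.** With SD 3.5 and 33 per arm, the standard error of the baseline difference is 3.5 × √(2/33) = 0.86. At r = 0.5, a one-standard-error imbalance moves a follow-up-only estimate by 0.5 × 0.86 = 0.43, and 0.43/2.46 is about 17% of the target effect. A change score moves by (1 − 0.5) × 0.86 = 0.43 in the opposite direction.

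**5. Type I error of choosing the test from the data.** In 20,000 simulated null trials with 33 per arm:

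| Data | Shapiro-Wilk pre-test decides | Smaller P value taken |
|---|---|---|
| Normal | 5.0% | 5.9% |
| Gamma | 5.0% | 6.5% |
| Lognormal | 5.0% | 6.8% |

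A separate check on lognormal change scores (r = 0.5, 6,000 replicates) gave 5.3% and 6.7%.

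**The case against.** The case for leaving the plan alone has five parts.

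- **Randomisation makes the unadjusted test valid.** This stands. A reader might infer that omitting age and blood pressure biases the treatment comparison. It does not in expectation; it costs precision and leaves chance imbalance uncorrected.
- **Blood pressure and baseline are not ignored.** This stands in part. Pulse pressure is the ΔP in the distensibility formula, and if change is tested, each patient serves as their own control. But the formula corrects for neither age nor pressure level, and a change score uses baseline less efficiently than a model does. The sentence on correction can also be read as background on arterial stiffness and not as an analysis commitment. That softens the contradiction without explaining why the comparison omits the correction.
- **The error rate is not seriously inflated.** This largely stands. A reader might infer that the plan runs at about 7%. That figure requires taking the smaller P value, which the article does not describe; it speaks of which analysis is appropriate. With no stated rule, free choice is not excluded, but it is the unfavourable scenario.
- **Power may be ample anyway.** All VEDERA patients are offered CADERA. If all 120 joined, 10% dropout would leave 120/2 × 0.9 = 54 per arm. On the one-year SD reading at r = 0.3, power would be 86% for change, 95% for follow-up only and 97% for ANCOVA. Uptake is unknown, so this limits the size of the loss but does not remove the point.
- **The confidence interval is not incompatible with a rank test.** This stands. A Hodges-Lehmann interval is in the same units and can accompany the rank-sum test. What remains is that the two routes estimate different things.

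It could also be said that covariates and a normality rule belong in a separate analysis plan. Here, though, the article itself names the two tests and makes the choice between them depend on the data, so the matter is fixed in the text and not merely deferred.

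**Conclusion.** The point holds as one of efficiency and prespecification. The article leaves the primary test and its estimand to the data, and does not make the age and blood pressure correction that it says the measure needs. The comparison remains valid under randomisation.

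At 33 per arm, the gain in power from baseline adjustment over the planned 80% is about 4 to 18 percentage points if 3.5 is the SD of one-year values and the alternative is a follow-up-only test. It is 6 to 14 points if 3.5 is the SD of change and the alternative is a change score. The 66% figure applies only to change scores at r = 0.3 under the first reading. All of these rest on assumed correlations of 0.3 to 0.7. Severity: should fix.

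**What to change.** Name one primary analysis: a linear model of one-year aortic distensibility on randomised arm, baseline distensibility, age and baseline mean arterial pressure, with heteroscedasticity-robust standard errors. Report the adjusted mean difference with its 95% confidence interval. Use baseline and not one-year pressure, so that any treatment effect on pressure is not adjusted away. The robust standard errors also remove the need to judge equal variances from the data.

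Keep a log-scale analysis or the Wilcoxon test with a Hodges-Lehmann interval as a named sensitivity analysis. Use the same form of model, with each outcome's own baseline, for the secondary and two-year outcomes.

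The cost is a few degrees of freedom and a paragraph of wording. The baseline scan is already planned, blood pressure is recorded at the scan, and age is known.

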## Methods/Design

### Study design

CADERA bolts on to the VEDERA (Very Early versus Delayed Etanercept in Rheumatoid Arthritis) trial, a prospective longitudinal intervention study of patients with early RA, randomized to either first-line TNFi therapy (etanercept, ETN) and MTX or optimal synthetic DMARD therapy. VEDERA is an investigator-initiated research (IIR) study based at the Leeds Institute of Rheumatic and Musculoskeletal Medicine, and is funded by an unrestricted educational grant that is part of an IIR agreement with Pfizer. VEDERA is a phase IV, single-centre study of 120 patients with new-onset, treatment-naïve RA, randomized to either immediate ETN and MTX combination or initial MTX and a treat-to-target regimen (optimal, standard conventional therapy approach); with step-up in the latter group to ETN and MTX combination therapy in patients failing to achieve a pre-defined target of remission after 24 weeks. The aim of VEDERA is to assess for the depth of remission (clinical and imaging) and immunological normalization induced by the treatment arms, as well as to identify predictors of remission.VEDERA patients will be recruited to CADERA and undergo CMR at baseline (prior to treatment) as well as after one and two years of treatment (see Figure 1). The change in CVD status as defined by CMR between baseline and follow-up in patients treated with early biological or optimal DMARD therapy will be determined. The study flow chart is presented in Figure 1. At the end of the study all patients will enter an inflammatory arthritis registry based at the National Institute for Health Research (NIHR) Leeds Musculoskeletal Biomedical Research Unit (LMBRU).

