### Enrolment criteria

Patients eligible for VEDERA will be recruited from the Leeds Teaching Hospitals NHS Trust Rheumatology service. The recruitment period is expected to last up to 36 months. All patients recruited to VEDERA will be offered inclusion to the CADERA study. CADERA CMR scans will be performed and analyzed at Leeds General Infirmary. The study will be performed in accordance with the Declaration of Helsinki (October 2000), with all patients providing informed written consent.

Inclusion criteria for VEDERA, and therefore CADERA, are patients diagnosed with RA according to the 2010 American College of Rheumatology/The European League Against Rheumatism (ACR/EULAR) criteria (Table 1), who have not yet received therapy with DMARDs, have early (symptoms for less than one year) active disease (clinical or imaging evidence of synovitis and Disease Activity Score in 28 joints with Erythrocyte Sedimentation Rate (DAS28-ESR) ≥3.2) and at least one poor prognostic factor (anti-citrullinated peptide antibody (ACPA) +/- abnormal power doppler in at least one joint).

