#### Missing data

The numbers of patients with missing data for one or more CMR measurements, and the number of uninterpretable images will be reported. Patients with missing data for any CMR measurement will be excluded from any comparison involving that measurement.

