## Trial status

This trial is ongoing. Patient recruitment and follow-up is underway. Recruitment began in February 2012 and is expected to end in June 2015.

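### The stated analysis time, the end of recruitment, is incompatible with the one-year primary endpoint and the two-year analysis; followed literally, it would cost precision

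*Protocol article*

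**What the plan says.** All of this is in the protocol article.

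- **Timing and population** (Sample size calculation, analysis paragraph): "All patients meeting eligibility criteria will be included in the analyses and these will be conducted at the end of the recruitment period".
- **Primary measurement** (Primary outcome measure): "It will be measured and quantified at baseline and at one year in each arm of the study".
- **Primary comparison** (Sample size calculation): "Both treatment arms will be compared with primary outcome aortic distensibility from baseline to one-year follow-up, as well as other outcome measures".
- **Two-year analysis** (same paragraph): "Treatment effects on secondary outcome measures and effects at the two-year follow-up point will be analyzed in an equivalent manner".
- **Incomplete data** (Missing data): "Patients with missing data for any CMR measurement will be excluded from any comparison involving that measurement".
- **Length of recruitment**: "The recruitment period is expected to last up to 36 months" (Enrolment criteria) and "Recruitment began in February 2012 and is expected to end in June 2015" (Trial status).
- **Parent trial size** (Study design): "VEDERA is a phase IV, single-centre study of 120 patients with new-onset, treatment-naïve RA". CADERA inclusion is offered to these patients, so 120 is an upper limit for CADERA.

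The article ties no analysis to the last one-year or two-year visit and gives no other data cut-off.

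**The concern.** The timing sentence makes two promises that cannot both be kept for the primary outcome. If every eligible patient is to be included, the analysis has to wait at least 12 months after the last enrolment. If the analysis is run when recruitment closes, the most recent recruits have only a baseline scan. The complete-case rule would then leave them out of the one-year comparison, and a still larger group out of the two-year comparison.

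This is more than a detail left to a separate analysis plan, because the article does fix an analysis time and that time does not fit its own endpoint. What is at stake is the number of patients contributing to the primary comparison, and therefore its power and the width of its confidence interval. It also leaves unclear which data cut was planned.

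**Working it through.** **1. The plan's own figures.** Inputs from Sample size calculation: difference 2.46, SD 3.5 (both in 10^-6 cm^2 dyne^-1), two-sided 5%, independent-samples t-test. With n per arm, the noncentrality is 2.46 / (3.5 × √(2/n)) on 2n − 2 degrees of freedom.

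- n = 26: power 70.0%
- n = 33: power 80.3%
- n = 44: power 90.3%

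These match the stated 26, 33 and 44. Dividing by 0.9 and rounding up gives 29, 37 and 49, against the stated 30, 38 and 50. That difference of one patient per arm does not matter here.

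**2. Share of patients without the scan when recruitment closes.** Under uniform accrual over M months, the share without one-year data is 12/M and the share without two-year data is 24/M. M is 36 from Enrolment criteria, or 40 to 41 from the dates in Trial status.

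| M (months) | No one-year scan | Of 120 | No two-year scan | Of 120 |
|---|---|---|---|---|
| 36 | 12/36 = 33.3% | 40 | 24/36 = 66.7% | 80 |
| 40 | 12/40 = 30.0% | 36 | 24/40 = 60.0% | 72 |
| 41 | 12/41 = 29.3% | 35 | 24/41 = 58.5% | 70 |

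**3. Power of the one-year comparison.** Evaluable per arm = enrolled per arm × (1 − 12/M) × 0.9. For 50 per arm and M = 36 this is 50 × 0.667 × 0.9 = 30.0. The noncentrality is then 2.46 / (3.5 × √(2/30)) = 2.72 on 58 degrees of freedom, which gives power of 76.3%. The same steps, with fractional n left unrounded, give:

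| Enrolled per arm | Evaluable, analysis after follow-up (10% dropout) | Power | Evaluable, analysis at recruitment close (M = 36 to 41) | Power |
|---|---|---|---|---|
| 60 (all 120, if 1:1) | 54 | 95% | 36.0 to 38.2 | 84% to 86% |
| 50 | 45 | 91% | 30.0 to 31.8 | 76% to 79% |
| 38 | 34.2 | 82% | 22.8 to 24.2 | 64% to 67% |
| 30 | 27 | 72% | 18.0 to 19.1 | 54% to 56% |

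**4. Two-year comparison.** Evaluable per arm = enrolled per arm × (1 − 24/M) × 0.9. For 50 per arm this is 50 × 0.333 × 0.9 = 15 at M = 36, and 50 × (17/41) × 0.9 = 18.7 at M = 41.

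**The case against.** The best defence is that the sentence is a slip for the end of follow-up. The same paragraph plans a two-year analysis, which cannot be complete when recruitment closes, and the same sentence promises to include all eligible patients. Read as a whole, the article presupposes analysis after follow-up. This is plausible, and it is why the losses above are conditional on a literal reading. It does not make the sentence correct, because nothing else in the article supplies the intended cut-off.

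It can also be said that a scan not yet due is not missing data in the ordinary sense. That is fair as a matter of wording, but a patient without a one-year value cannot enter a one-year comparison however the absence is labelled.

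A reader might infer more than the documents support:

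- **That the trial will lose about 30% of its patients.** This needs both the literal reading and uniform accrual. Front-loaded accrual would reduce the figure and back-loaded accrual would raise it.
- **That the stated power is lost.** The article lists 70%, 80% and 90% scenarios without choosing one. If all 120 parent-trial patients join, power stays above 80% even on the literal reading. It falls short of the matching scenario at 50 or 38 per arm, and the article does not say which number CADERA will reach.
- **That the type I error is inflated by a second look.** No section plans to test the one-year outcome twice. The two-year analysis is a separate, planned time point.
- **That the treatment comparison is biased.** Loss determined by enrolment date is administrative and, under randomisation, should be similar in both arms.

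**Conclusion.** The point stands as an error in the stated timing that should be fixed. That patients enrolled in the last 12 or 24 months cannot yet have the scan follows from the article's text alone and needs no assumption.

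The size does rest on assumptions: literal application of the sentence, uniform accrual over 36 to 41 months, 10% dropout acting in addition to the timing loss, and the plan's own effect and SD. On these, the timing loss at one year is about three times the dropout allowance, and power falls by roughly 10 to 18 percentage points depending on enrolment. The consequence is reduced precision. Because the sentence may well be a slip and the loss is balanced between arms, this does not threaten the validity of the comparison.

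**What to change.** Keep the commitment to include all eligible patients and replace the timing clause with:

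*The primary analysis will be conducted once, after the last randomised patient's one-year CMR has been read and the data locked; the two-year analysis will be conducted after the last two-year CMR; only baseline descriptive analyses may be run at the end of recruitment.*

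The cost is one sentence. It needs no extra patients or scans. The primary result arrives about 12 months after recruitment closes, a wait that the follow-up schedule already imposes. The change should be made before any comparison of the arms is run.

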### Sample size calculation

Power calculations are based on a previous study by Ikonomidis *et al*. [28]. We assumed an effect size of 2.46 cm^2^dyne^-1^10^-6^, representing 75% of the difference between treated (Anakinra) and non-treated RA patients reported by Ikonomidis *et al*. [28]. Mean aortic distensibility at baseline to post-treatment for treated and non-treated patients was 1.56 cm^2^dyne^-1^10^-6^ and 4.6 cm^2^dyne^-1^10^-6^, respectively. The standard deviation (SD) of the post-treatment measurements in the Anakinra group was 3.2 cm^2^dyne^-1^10^-6^ and a more conservative estimate of 3.5 cm^2^dyne^-1^10^-6^ has been used in the CADERA power calculation. Assuming an SD of 3.5 cm^2^dyne^-1^10^-6^, a power of 70%, 80% and 90% would be achieved at 5% significance level in a two-tailed independent samples Student’s t-test with 26, 33 and 44 patients respectively in the primary outcome measure of aortic distensibility in each treatment group (30, 38 and 50 when adjusted for 10% dropout).

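### Comorbidity subgroups are to be analysed separately, and no interaction named in the protocol clearly tests whether the treatment effect differs by comorbidity

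*Protocol article*

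**What the plan says.** The plan for subgroups is in the analysis paragraph under Sample size calculation in the protocol article. It reads "Exploratory subgroup analyses will be conducted separately by other comorbidities, a maximum of two to three that are clinically plausible", and adds that an appropriate multiple-testing correction will be made. The correction is not specified, the comorbidities are not named and no prevalence is given.

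The next sentence reads "Interactions between subgroups and interactions between CMR findings and biomarkers will be explored through building a linear model with interaction terms". Two kinds of interaction are named: one between subgroups, and one between CMR findings and biomarkers. Treatment arm is in neither.

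Under Primary outcome measure, the article says that arm differences will be presented at P below 0.05 with a 95% confidence interval.

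**The concern.** Whether a comorbidity modifies the treatment effect is a question about the difference between two treatment differences. One term answers it: treatment arm by comorbidity, fitted to all patients. Running the arm comparison separately in patients with and without the comorbidity gives two P values, and neither tests that difference.

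A significant result in one stratum and a non-significant one in the other is what low and unequal power produces when the effect is the same in both. A multiplicity correction guards against false positives when there is no effect. It does not address a split result under a real, uniform effect, because that split comes from stratum size.

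At stake is a subgroup statement in the trial report that the data cannot support. The primary comparison is unaffected.

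**Working it through.** **Inputs from the protocol article (Sample size calculation).** Test: "at 5% significance level in a two-tailed independent samples" t-test. Difference: "We assumed an effect size of 2.46 cm^2^dyne^-1^10^-6". SD and power: "Assuming an SD of 3.5 cm^2^dyne^-1^10^-6^, a power of 70%, 80% and 90% would be achieved". Size: "with 26, 33 and 44 patients respectively in the primary outcome measure of aortic distensibility in each treatment group".

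**Assumptions of this check.** Comorbidity prevalence 20%, 30% or 40%, equal in both arms; SD 3.5 within each stratum; the same true effect in everyone; 33 evaluable patients per arm (the plan's 80% case).

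**Step 1: the plan's own figure.** For n per arm, the noncentrality is δ / (SD × √(2/n)) on 2n − 2 degrees of freedom. With δ = 2.46 and SD = 3.5, power is 70.0% at n = 26, 80.3% at n = 33 and 90.3% at n = 44. The stated 26, 33 and 44 are reproduced.

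**Step 2: power within strata.** The same formula is applied to each stratum. The strata contain different patients, so the two tests are independent, and

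P(exactly one significant) = p₁(1 − p₂) + p₂(1 − p₁).

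| Prevalence | Per arm, with v without | Power at 0.05 | Split at 0.05 | Split at 0.05/6 |
|---|---|---|---|---|
| 20% | 7 v 26 | 22.8% v 70.0% | 60.9% | 43.4% |
| 30% | 10 v 23 | 31.9% v 64.5% | 55.2% | 39.4% |
| 40% | 13 v 20 | 40.5% v 58.2% | 51.5% | 36.8% |

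First row: 0.228 × 0.300 + 0.700 × 0.772 = 0.068 + 0.540 = about 0.61. The divisor 6 is three comorbidities with two strata each.

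**Step 3: direction.** The misleading result most easily pictured is that only the larger stratum is significant. Its probability at 0.05 is p₂(1 − p₁):

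- 20%: 0.700 × 0.772 = 54%
- 30%: 0.645 × 0.681 = 44%
- 40%: 0.582 × 0.595 = 35%

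**Step 4: half the design effect.** With δ = 1.23 and no correction, the split probability at 33 per arm is 28.6%, 28.0% and 27.7% at the three prevalences.

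**Step 5: larger samples.** The parent trial has 120 patients, so 60 per arm is the ceiling. At 20% prevalence (12 v 48) and the full effect, the split probability is 60.5% at 0.05 and 69.1% at 0.05/6. Correction lowers it at 33 per arm and raises it here, so it is not a dependable safeguard.

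**Step 6: the interaction test.** Under a uniform effect, the treatment-by-comorbidity term is falsely significant at its nominal 5% (4.5% to 5.1% in 10,000 simulated trials per setting). Its cost is power. The standard error is 3.5 × √(2/n₁ + 2/n₂): 2.11 for 7 v 26, 1.87 for 10 v 23 and 1.76 for 13 v 20. If the effects truly differed by 2.46, power on 62 degrees of freedom would be 21%, 25% and 28%, before any correction.

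**The case against.** The strongest reply is that the right test may already be planned. The sentence on interactions follows directly on the subgroup sentence, and in a two-arm trial a loose phrase about interactions between subgroups could mean a test of whether effects differ between them. Conducting the analyses separately could also mean one comorbidity at a time, and no within-stratum t-test is spelled out. This ambiguity is real and stands. It does not remove the point: promising a multiplicity correction implies that P values will be produced, the text leans towards separate analyses, and treatment arm is not mentioned.

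The analyses are also labelled exploratory, limited to two or three plausible factors, and accompanied by confidence intervals. That stands too, and it makes the point minor.

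A third reply is that 5% for one interaction test is not like for like with a family of subgroup tests. It is fair. Simulation at 33 to 60 per arm, with independent comorbidities at 20% to 50% prevalence, gives about 4% to 7% for any false signal over two or three interaction tests with Bonferroni, and 8% to 18% without. At least one split result under separate testing occurs in 50% to 92%. The contrast survives.

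A reader might also infer that the CMR-by-biomarker interaction is ill-posed. The documents do not support this. The Biomarkers section speaks of linking biomarkers to CMR measurements without fixing which is the outcome, and the section on annual follow-up links CMR findings to clinical outcome, where a CMR finding could be a predictor.

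**Conclusion.** The point holds as a minor one. As worded, the protocol does not name the test that a claim of effect modification needs, and the wording that might stand for it is unclear. If such claims rested on separate tests, a uniform effect would often look comorbidity-specific: about 52% to 61% of trials uncorrected and 37% to 43% with Bonferroni over six tests, at the plan's full effect with 33 per arm. These figures depend on assumed prevalences of 20% to 40%, which the documents do not give.

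A reader might infer that a misleading split would occur more often than not. That cannot be said in general. It fails for one comorbidity at 33 per arm under Bonferroni over six tests, and at half the design effect.

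A reader might also infer that the report will say TNFi helps only patients without the comorbidity. No such rule of inference is planned, and that particular direction has probability 54%, 44% and 35% uncorrected. Nor do the exclusions for known CVD and severe comorbidity establish that the comorbid strata will be small.

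**What to change.** State in the analysis text that any claim of effect modification rests on a treatment-by-comorbidity interaction term, fitted in one linear model on all patients, one for each of the two or three comorbidities. Apply the multiplicity correction to those two or three interaction tests. Report subgroup-specific treatment differences with 95% confidence intervals as description only, without within-subgroup significance claims. If the phrase about interactions between subgroups was meant as this test, replace it with wording that names treatment arm.

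The cost is one or two sentences and no new data. The drawback is the low power shown above: most of these analyses will report no evidence of a difference, which should not be read as evidence that the effect is uniform.
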